## Results

Data collection was completed in October 2020 and data are being prepared to be analyzed. Overall, 63.8% (286/448) of individuals completed the material in the OurRelationship coach condition, 53.8% (155/288) of couples completed the OurRelationship contingent coach condition, and 54.5% (157/288) of individuals completed the OurRelationship automated (ie, email only) condition. Similarly, 69.4% (306/441) of couples completed the content in the ePREP coach condition, 74.2% (210/283) completed the content in the ePREP contingent coach condition, and 66.2% (188/284) of couples completed content in the ePREP automated (ie, email only) condition. Currently, no other outcomes except for completion rates have been analyzed. Given the large sample size within and between conditions, the current sample is large enough to identify potential predictor variables and evaluate their prediction accuracy. This study is expected to conclude in the summer of 2022.

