**Methods:**

To accomplish these goals, this project intends to use data from a web-based Sequential Multiple Assignment Randomized Trial of the OurRelationship and web-based Prevention and Relationship Enhancement programs, in which the method and type of coach contact were randomly varied across 1248 couples (2496 individuals), with the hope of advancing theory in this area and generating accurate predictions. This study was funded by the US Department of Health and Human Services, Administration for Children and Families (grant number 90PD0309).

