## Methods

### Procedure

This study was funded by the US Department of Health and Human Services, ACF (grant number 90PD0309; see Multimedia Appendix 1 for peer reviews). The parent study was registered with ClinicalTrials.gov (NCT02806635). The analyses and project design for this study will be preregistered with the Open Science Framework to promote accountability. Data for this study come from a large (N=1248 couples; N=2496 individuals) web-based RCT with a Sequential Multiple Assignment Randomized Trial design [44]. Sequential Multiple Assignment Randomized Trial designs are experiments that allow researchers to develop adaptive interventions and reassign nonadherent participants [44]. This was done by varying the levels and types of coach contact that a couple receives. In this study, couples were initially assigned to one of five conditions: OurRelationship coach, OurRelationship automated (email only), ePREP coach, ePREP automated (email only), and the waitlist control condition. However, couples initially assigned to the no-coach condition that did not complete scheduled web-based activities for >2 weeks underwent a second randomization: to continue the program without a coach or to be assigned to a coach for the remainder of the program. Those who were randomized to continue without a coach were still allowed to access the program, complete the activities, and were still sent automated reminders. In contrast, those who were randomly reassigned to receive coach contact were emailed by a coach and invited to schedule a call. Couples in this contingent coach condition received up to 3 additional calls (for a maximum of 4 calls) depending on where in the program they were when they stopped making adequate progress. This full variability of possible coaching contact, all of which involved random assignment, will allow us to determine the most powerful predictors of which couples should receive 4 15-minute coach calls, those who should simply receive emails, and those who should receive contingent coach contact after displaying patterns of treatment nonadherence.

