### Participants

A total of 226 couples were randomly assigned to the OurRelationship coach condition, 145 couples were assigned to the OurRelationship contingent coach condition, and 145 couples were assigned to the OurRelationship automated (ie, email only) condition. Similarly, 222 couples were assigned to the ePREP coach condition, 143 couples were assigned to the ePREP contingent coach condition, and 143 couples were assigned to the ePREP automated (ie, email only) condition. A total of 224 couples were assigned to the waitlist control condition. In total, 4 individuals from the OurRelationship coach condition, 2 from the OurRelationship contingent coach condition, and 2 from the OurRelationship automated condition asked to discontinue and have their data removed from the study. Furthermore, 3 individuals from the ePREP coach condition, 2 from the ePREP contingent coach condition, and 3 from the ePREP automated condition asked to discontinue and have their data removed from the study.

In total, 47.5% (1178/2480) of the sample identified as male, and 52.5% (1302/2480) of the sample identified as female. The average length of the relationship was 5.74 years (SD 5.18). Most of the participants reported belonging to an opposite-gender relationship (2318/2480, 93.47%), and a smaller percentage were in same-gender relationships (162/2480, 6.53%). Most participants identified as White non-Hispanic (1520/2480, 61.29%), fewer identified as Black (434/2480, 17.5%), White Hispanic (279/2480, 11.25%), Black Hispanic (28/2480, 1.13%), American Indian or Alaskan Native (23/2480, 0.93%), Asian (17/2480, 0.69%), Hawaiian or Pacific Islander (4/2480, 0.16%), and Biracial (86/2480; 3.47%); and 3.59% (89/2480) of participants belonged to a race that was not listed. Furthermore, 6.81% (169/2480) of participants did not have a degree or diploma, 12.3% (305/2480) had earned a general education diploma, 14.23% (353/2480) had completed high school, 8.23% (204/2480) had a technical or vocational certification, 22.54% (559/2480) had some college degree, 8.83% (219/2480) had graduated with an associate’s degree, 10.69% (265/2480) had a bachelor’s degree, and 2.38% (59/2480) had a master’s or advanced degree.

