### Data Analysis

In an effort to reduce computational complexity, rather than using individual responses, responses from both members of the couple will be combined in the average score for the couple for each of the continuous predictor variables listed above as well as the continuous outcome variable (ie, relationship satisfaction).

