These models will be built using the random forest algorithm [52]. The random forest algorithm reduces overfitting by bootstrapping or fitting several different trees to subsets of the sample to inform the predictions (ie, bagging) [52]. Once the ensemble of trees is generated, the outputs from all the trees are aggregated, and the prediction is generated. Its ability to predict treatment outcomes for individuals and couples has been proven in several precision medicine studies [13,14]. Thus, in the first aim of this study, the random forest algorithm will be used to accurately predict the within-group likelihood that a couple completes the OurRelationship and ePREP programs in (1) the full-coach condition, (2) the automated coaching condition, and (3) the contingent coach condition as well as the magnitude of their gains in relationship satisfaction. The model characteristics address the model performance on the test data set*.* For binary outcomes (program completion), the model characteristics used to evaluate the validity of the model include sensitivity, specificity, positive predictive value, and negative predictive value of the model built on the test data set (Figure 1). Model sensitivity is measured by the percentage of true positives (ie, a/a+c). Model specificity is the percentage of true negatives (ie, d/d+b). A model’s positive predictive value yields a positive test result and the probability that the participant will complete the program (ie, a/a+b). Finally, a model’s negative predictive value yields negative test results and the probability that the participant will not complete the program (ie, d/d+c). Good models for binary outcomes include models whose sensitivity, specificity, positive predictive value, and negative predictive value are closest to 1. For continuous outcomes (ie, improvements in relationship satisfaction), model accuracy will be evaluated using the RMSE. The RMSE is a measure of absolute fit and is the square root of the variance of the residuals; smaller values indicate better fit.

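### Results calls the sample large enough to evaluate prediction accuracy, but accuracy is scored on part of each arm's couples; scoring every couple would tighten it at almost no cost

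*Protocol article*

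**What the plan says.** The sample is introduced under Procedure as a "large (N=1248 couples; N=2496 individuals) web-based RCT", and Results closes its report of completion rates with the adequacy statement: "Given the large sample size within and between conditions, the current sample is large enough to identify potential predictor variables and evaluate their prediction accuracy". The article gives no effect size, power or interval width in support.

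Four other places fix what the evaluation will rest on:

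- **Unit.** Program Completion codes one result per couple. Data Analysis adds that "responses from both members of the couple will be combined in the average score for the couple for each of the continuous predictor variables", and treats relationship satisfaction in the same way.
- **Arms.** Participants lists them by couple. OurRelationship has 226 in its coach arm; for the other two arms, "145 couples were assigned to the OurRelationship contingent coach condition, and 145 couples were assigned to the OurRelationship automated". ePREP has 222 in its coach arm; for the other two, "143 couples were assigned to the ePREP contingent coach condition, and 143 couples were assigned to the ePREP automated (ie, email only) condition". The waitlist has 224.
- **Number of models.** The plan for Aim 1 fits three sets of models by coaching level if a preliminary comparison lets program be ignored, and six sets (program by coaching level) if it does not.
- **Where accuracy is read.** The same section says: "The model characteristics address the model performance on the test data set". The measures are sensitivity, specificity, positive and negative predictive value (PPV and NPV) and, for satisfaction, root mean square error (RMSE).

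**The concern.** The headline figure is 1248 couples, but no accuracy estimate uses more than a fraction of one arm. Three reductions apply in turn: couples rather than individuals, one arm at a time, and the test portion of that arm. Specificity is reduced once more, because only non-completers contribute to it, and they are the minority in every arm.

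Prediction accuracy is the result of Aim 1, and the plan for Aim 3 goes ahead on the assumption that the earlier models predict adequately. If the interval around specificity spans several tens of points, a reader cannot judge whether a model is good enough to carry forward. The adequacy sentence tells that reader there is no such problem.

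**Working it through.** The plan has no precision or power figure to reproduce, so the check starts from its counts.

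**1. Couples per model (Participants).** Program arms: 226 + 145 + 145 + 222 + 143 + 143 = 1024. With the 224 waitlist couples this gives 1248, as stated. Pooled over program: full 226 + 222 = 448; contingent 145 + 143 = 288; automated 145 + 143 = 288.

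**2. Non-completion (Results).** The printed denominators are essentially counts of individuals, although some are labelled couples (for example 2 × 226 − 4 = 448). I assume that couples fail to complete at the printed rates:

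- OurRelationship: full 162/448 = 36.2%; contingent 133/288 = 46.2%; automated 131/288 = 45.5%.
- ePREP: full 135/441 = 30.6%; contingent 73/283 = 25.8%; automated 96/284 = 33.8%.

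Couples × rate gives the non-completing couples in each arm; for example 143 × 0.258 = 36.9 in ePREP contingent. Pooled: full 81.7 + 68.0 = 149.7; contingent 67.0 + 36.9 = 103.9; automated 66.0 + 48.3 = 114.3.

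**3. Half-width for specificity.** With m non-completers scored and an assumed true specificity of 0.60, the 95% half-width is 1.96 × √(0.24/m). The test share is not stated, so 20%, 30% and 50% are shown, with 100% meaning that every couple is scored.

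| Model | Couples | Non-completers | 20% | 30% | 50% | 100% |
|---|---|---|---|---|---|---|
| Full, pooled | 448 | 149.7 | ±17.5 | ±14.3 | ±11.1 | ±7.8 |
| Contingent, pooled | 288 | 103.9 | ±21.1 | ±17.2 | ±13.3 | ±9.4 |
| Automated, pooled | 288 | 114.3 | ±20.1 | ±16.4 | ±12.7 | ±9.0 |
| OurRelationship contingent | 145 | 67.0 | ±26.2 | ±21.4 | ±16.6 | ±11.7 |
| OurRelationship automated | 145 | 66.0 | ±26.4 | ±21.6 | ±16.7 | ±11.8 |
| ePREP contingent | 143 | 36.9 | ±35.4 | ±28.9 | ±22.4 | ±15.8 |
| ePREP automated | 143 | 48.3 | ±30.9 | ±25.2 | ±19.5 | ±13.8 |

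Worked case: ePREP contingent at 30% has 143 × 0.30 = 43 test couples, of whom 36.9 × 0.30 = 11.1 are non-completers. Then 1.96 × √(0.24/11.1) = 0.289.

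**4. Sensitivity to the assumptions.**

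- Wilson intervals give ±25 rather than ±29 points in the worked case, and ±29 rather than ±35 at a 20% share.
- At a true specificity of 0.75, every entry is multiplied by √(0.1875/0.24) = 0.88.

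**5. RMSE.** The relative 95% half-width is about 1.96/√(2m), where m is the number of couples scored. At a 20% share this is about 15% to 18% with three models (90 and 58 couples) and 26% in the smallest arms (29 couples). With every couple scored it is about 7% to 8% and 12%.

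**The case against.** Several objections have force.

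- **The test share is an assumption.** An article may leave it to the full plan, so its absence is no fault. However, any test set that is only part of an arm loses precision against scoring the whole arm.
- **The largest widths belong to one branch.** Six models arise only if the program comparison rejects. With three models the imprecision is moderate.
- **The completion rates may err.** If a couple counts as complete only when both partners finish, non-completers are at least as many as assumed. The specificity intervals would then be the same or narrower.
- **Finding predictors within pooled arms is reasonable.** By a simple correlation test, 80% power is reached from about r = 2.80/√448 = 0.13 to 2.80/√288 = 0.17.

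A reader might also infer more than the documents support:

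- *That Aim 3 is underpowered by a stated amount, so that null moderators will be misread.* Comparing correlations between two arms would give low power for small differences, but Aim 3 does not do that. It predicts each couple's outcome under each condition and fits a second forest to the predicted differences. Those differences are functions of the baseline variables and carry no couple-level residual noise, so the procedure could as easily declare too many moderators as too few. Nor does the article say that a null will be read as no effect.
- *That adequacy was judged on individuals.* Couple counts and couple averaging are stated openly, and Results does not say which count the judgement used.

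**Conclusion.** The point holds for the evaluation of accuracy. Results asserts adequacy without qualification, while accuracy is estimated on a part of each arm's couples. With a test share of 20% to 50%, couple completion at the printed rates and a true specificity of 0.60, the half-width for specificity is about 11 to 21 points with three models. It is about 17 to 35 points in the four smallest arms with six. Even the favourable 50% split leaves 17 to 22 points in those four arms.

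The article states no power or precision target that the design misses, so this is not a failed sample-size calculation. It is an unqualified claim combined with an evaluation that discards precision the data could supply. No power figure for Aim 3 follows from this check.

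**What to change.** 1. **Data Analysis Plan for Aim 1.** Replace test-set scoring with out-of-bag or k-fold cross-validated predictions, so that each couple in an arm is scored by trees or models that did not use it. Do any tuning, and the imputation described under Missing Data, inside the folds. Report sensitivity, specificity, PPV, NPV and RMSE with 95% confidence intervals. Under the assumptions above, specificity narrows to about ±8 to 9 points (three models) or ±12 to 16 points (smallest six-model arms). The plan for Aim 2 already uses out-of-bag data for variable importance, so no new method is needed.

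2. **Results.** Replace the adequacy sentence with the couples per model (448, 288, 288; or 226, 222, 145, 145, 143, 143) and the expected interval widths. Describe the between-condition predictors as exploratory, especially if six models are used. Do not present power or detectable differences from a two-arm correlation test as properties of the Aim 3 procedure. Do not give 1024 as the number analysed in Aim 3, because the aims name the waitlist as a comparator.

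The cost is computing time and a few sentences. No new data are needed, and Results reports that only completion rates have been analysed so far. The stated adequacy will read less favourably.

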## Discussion

One of the direct benefits of this study will accrue to social services programs and program administrators of web-based relationship education. The results of this study will allow for more effective tailoring of coach contact to better meet the needs of unique low-income couples experiencing relationship distress. A second benefit is the improvement of web and evidence-based interventions. The federal government is increasing emphasis on delivering evidence-based interventions and, given the social distancing regulations put in place because of COVID-19, participation in web-based programs will likely increase either as an initial intervention or as a backup intervention in cases where in-person services are suspended. Thus, it is important that web-based federal services are as effective and accessible as possible. Overall, this study hopes to help practitioners by generating accurate predictions to match unique couples to the level of web-based programming that will help them to obtain the maximal benefit.

## Appendix

Multimedia Appendix 1 Peer-reviewer report from the Administration for Children & Families (USA).

## Abbreviations

ACF: Administration for Children and Families
ePREP: web-based Prevention and Relationship Enhancement Program
IPV: intimate partner violence
RCT: randomized controlled trial
RMSE: root mean square error
VIMP: variable importance
